## Abstract

**Background:**

Deaths due to injuries exceed 4.4 million annually, with over 90% occurring in low-and middle-income countries. A key contributor to high trauma mortality is prolonged trauma-to-treatment time. Earlier receipt of medical care following an injury is critical to better patient outcomes. Trauma epidemiological studies can identify gaps and opportunities to help strengthen emergency care systems globally, especially in lower income countries, and among military personnel wounded in combat. This paper describes the methodology of the “Epidemiology and Outcomes of Prolonged Trauma Care (EpiC)” study, which aims to investigate how the delivery of resuscitative interventions and their timeliness impacts the morbidity and mortality outcomes of patients with critical injuries in South Africa.

**Methods:**

The EpiC study is a prospective, multicenter cohort study that will be implemented over a 6-year period in the Western Cape, South Africa. Data collected will link pre- and in-hospital care with mortuary reports through standardized clinical chart abstraction and will provide longitudinal documentation of the patient’s clinical course after injury. The study will enroll an anticipated sample of 14,400 injured adults. Survival and regression analysis will be used to assess the effects of critical early resuscitative interventions (airway, breathing, circulatory, and neurologic) and trauma-to-treatment time on the primary 7-day mortality outcome and secondary mortality (24-h, 30-day) and morbidity outcomes (need for operative interventions, secondary infections, and organ failure).

**Discussion:**

This study is the first effort in the Western Cape of South Africa to build a standardized, high-quality, multicenter epidemiologic trauma dataset that links pre- and in-hospital care with mortuary data. In high-income countries and the U.S. military, the introduction of trauma databases and registries has led to interventions that significantly reduce post-injury death and disability. The EpiC study will describe epidemiology trends over time, and it will enable assessments of how trauma care and system processes directly impact trauma outcomes to ultimately improve the overall emergency care system.

*Trial Registration*: Not applicable as this study is not a clinical trial.

## Background

### The global burden of injury

Intentional and unintentional injuries are a leading cause of mortality worldwide, claiming over 4.4-million lives annually [1]. The World Health Organization has ranked motor vehicle collisions, falls, and interpersonal violence within the top 20 global causes of death and disability [1, 2]. Further, a large proportion of trauma deaths occur prior to arrival at a hospital [3, 4]. To significantly reduce global trauma mortality, there is an immediate need to improve patient-level outcomes in prehospital and in-hospital settings, in concurrence with prevention efforts. Prehospital care (e.g., basic care in ambulances) is especially critical in averting poor outcomes at the population level because it represents the earliest formal opportunity for the emergency care system to initiate life-saving care [5].

Trauma disproportionately impacts populations in low-and middle-income countries (LMICs) with over 90% of global injury-related deaths occurring in these populations [6, 7]. Individuals residing in low-resource settings experience twice the trauma mortality of high-resource settings, partly due to poor access and delays in receiving critical resuscitative interventions (CRI) and definitive trauma care [8–12]. South Africa, specifically, has a transportation-related fatality rate (39.7 per 100,000) that is twice the global average and mortality from interpersonal violence that is among the highest in the world, both of which are partially due to prolonged duration from time of injury to definitive care [11]. There is an urgent need to improve emergency care systems in South Africa via comprehensive trauma epidemiological studies. These population-based studies that collect individual patient-level data can inform clinical care and policies to maximally impact populations, thus making them an essential first step to reducing the burden of trauma [6, 13].

### The burden of trauma in U.S. military populations

In addition to civilian populations, trauma is a major cause of morbidity and mortality amongst military populations. Battlefield hemorrhage, for example, is the leading cause of fatalities with potentially survivable injuries amongst U.S. military personnel [14, 15]. Yet only one-in-four combat fatalities is estimated to have potentially survivable injuries, and outcomes depend on the timely delivery of early prehospital CRIs [4]. Several urban, U.S.-based civilian prehospital trauma studies have been conducted in relatively small samples of patients and report relatively short transport times to definitive care [16, 17], thus generalizability and relevance to the battlefield are limited. The trauma profile of the Western Cape in South Africa, due to gang “wars” and interpersonal firearm violence, for example, better reflects the military paradigm of severe injury patterns, health system resource limitations, and prolonged trauma-to-treatment time [18]. Thus, epidemiologic studies conducted in this region can provide important findings for use in military triage and transport decisions.

### The impact of delayed care on morbidity and mortality

To yield the best outcomes after critical injuries in both civilian and military settings, patients should receive prompt treatments at the point of injury and rapid transport directly to a capable trauma center [4, 19, 20]. Delays experienced between the time of injury to arrival at a surgically capable trauma facility negatively impact outcomes for patients with severe injury [21]. In civilian contexts worldwide, delays are predominantly due to slow prehospital response or transport, or lengthy times spent in an initial non-trauma center. In U.S. urban and rural areas, studies have shown an inverse correlation between prehospital time and survival in motor vehicle victims [22]. Moreover, those in U.S. rural areas are 50% more likely to die from all-cause trauma compared to their urban counterparts because of longer prehospital transport times [22]. Studies examining the effects of prehospital time on mortality are sparse, with even fewer conducted in LMICs [9, 19, 23–27]. Within the U.S. military’s Africa Command area of operations, transportation times are frequently prolonged, which potentially worsens trauma outcomes [28–30]. To improve survival in battlefield situations where the duration of prehospital casualty care is prolonged, military trauma experts have called for scientific evidence to better inform clinical guidelines [31].

### The epidemiology and outcomes of prolonged trauma care (EpiC) study

To address scientific gaps in both global civilian public health and military medicine, the United States Department of Defense (DOD) funded the study “Epidemiology and Outcomes of Prolonged Trauma Care (EpiC): A Multicenter Prehospital Observational Study in the Western Cape of South Africa” [32, 33]. EpiC aims to advance the understanding of epidemiology and outcomes of trauma and will guide future interventional research. This will be the first multi-institutional trauma database to be implemented in South Africa that prospectively collects trauma case data from point of injury to outcome, linking pre- and in-hospital care with mortuary data. EpiC will inform public health officials and key stakeholders with evidence on how trauma treatments and system processes directly impact changes in patient outcomes, including trends in trauma epidemiology and care over time. Collecting longitudinal data with key time stamps from the public emergency care system across multiple regions and facility types will allow for comprehensive comparisons between patient sub-populations and outcomes [6, 34]. The EpiC study will determine how delivery of critical resuscitative interventions and the timeliness of these interventions impacts the morbidity and mortality of civilian patients in the Western Cape who experience significant trauma.

## Methods and design

### Objectives

The specific objectives of the EpiC study are:To assess the effect of delivery and timeliness of critical resuscitative interventions (CRI) on the primary 7-day mortality outcome and secondary mortality (24-h, 30-day) and morbidity outcomes (need for operative interventions, secondary infections, and organ failure).To assess the effect of individual resuscitative interventions (airway, breathing, circulatory, and neurologic) on similar mortality and morbidity outcomes.

We hypothesize that failure to deliver CRIs and longer durations of trauma-to-CRI time will be associated with increased risk of mortality and worse morbidity outcomes.

### Study setting

South Africa is an upper-middle income country with disparate trauma outcomes based on sex, socio-economic status, unemployment, urbanization, and race [11]. A call for urgent action by numerous public health and subject matter experts has been made to improve emergency care systems, both in South Africa as a whole, and in the Western Cape specifically [13]. EpiC will be implemented in a cross-section of the Western Cape emergency care system, in government-operated institutions and agencies. Study sites will include two district hospitals, one regional hospital, and their referral trauma center. EpiC will also include four Western Cape Government Emergency Medical Services (WCG EMS) ambulance bases and two forensic pathology laboratories that serve all four hospitals (Table 1, Fig. 1).

**Table 1 Tab1:** Characteristics of EpiC study sites

Institution/Agency	Level of care/Facility type	Number of sites	Community served	Distance to trauma center (km)	Number of hospital beds
Tygerberg	Tertiary trauma center	1	Urban	0	1384
Khayelitsha	District hospital	1	Urban	26.7	230
Ceres	District hospital	1	Rural	125.5	28
Worcester	Regional hospital	1	Rural	96.0	277
WCG EMS	Government ambulance	4	Urban, Rural	n/a	n/a
Forensic Pathology Service (FPS)	Government pathology service	2	Urban, Rural	n/a	n/a

n/a = not applicable; WCG EMS = Western Cape Government Emergency Medical Services

**Fig. 1 Fig1:**
[figure not shown]
Relative transport distances from EpiC study sites to the tertiary trauma care center (Tygerberg Hospital)

Tygerberg Hospital is the tertiary trauma (referral) center that provides specialty surgical and trauma care to a catchment area of 3.4 million people and attends to over 107,000 admissions annually of which 12,000–15,000 are seriously injured persons [35, 36]. All other EpiC hospital sites (Khayelitsha, Ceres, and Worcester Hospitals) refer complex and critical trauma patients to Tygerberg Hospital for a full range of trauma subspecialty care and consultations [37]. Khayelitsha Hospital is a frontline, district level facility that serves a dense urban catchment area of over 400,000 people and treats around 3,000 patients per month in the Emergency Center, many with injuries from interpersonal violence and motor vehicle collisions [38–40]. Worcester Hospital is a regional level facility that serves a rural population of 917,000 and can provide intensive care and general surgical care. Ceres Hospital is a rural, small district level facility without specialist physicians and offers basic trauma care. Patients at Ceres Hospital who require sub-specialty trauma and surgical care are stabilized and transferred to a trauma center by WCG EMS ambulances.

The WCG EMS is a public prehospital agency that annually treats and transports over 500,000 patients to hospitals, 40% due to trauma [41, 42]. Most ambulances are staffed by basic and intermediate life support providers, whereas advanced life support capable crews are reserved for the most critically injured patients [41, 42]. EpiC will include ambulances servicing catchment areas of the four participating hospitals. The Forensic Pathology Service (FPS) of the Western Cape has a constitutional mandate to perform autopsies on all unnatural deaths, including all trauma deaths. Two FPS labs will participate in this study: the Tygerberg FPS lab (includes deaths of patients from Tygerberg and Khayelitsha Hospital) and the Worcester FPS Lab (includes Worcester and Ceres Hospital deaths) [43].

### Study design

This is a prospective, multicenter cohort study of trauma patients that will be conducted over a 6-year period, divided into 3 phases: a preparatory Phase 1 (year 1), a pilot implementation Phase 2 (year 2), and a main study Phase 3 (years 3–6).

***Phase 1. ***During the preparatory phase, we will create an evidence-based, expert-consensus data dictionary and data capture tools. This process will involve a review and adaptation of five international high-quality trauma data dictionaries (DOD Trauma Registry [44], National Emergency Medical Services Information System [45], National Trauma Data Standard [46], Pan-Asian Trauma Outcomes Study [47], and World Health Organization dataset for injury [48]), a scoping review of literature published in the past 10 years [49], and a modified Delphi consensus-building process using a panel of 20 military and civilian trauma clinical and research experts.

***Phase 2. ***We will conduct a pilot study at all study sites to assess the feasibility of implementation, data collection, and analysis. During this phase we will enroll ~ 1,000 patients with moderate and high acuity trauma (using the South Africa Triage Scale [SATS] acuity score), assess the frequency of erroneous and missing data, and conduct preliminary data analyses to describe the study cohort [50].

***Phase 3.*** In the main study, we will prospectively collect data from all study sites and perform statistical analyses to answer the research objectives.

### Inclusion and exclusion criteria

The EpiC study will include adult patients aged 18 years and older with a clinical encounter for a traumatic injury at one or more of our 10 study sites. Eligible patients will meet one of the following criteria: (1) arrive and/or depart by WCG EMS to/from a participating site, (2) transported via WCG EMS with initial signs of life or receive prehospital resuscitation care, but die in the ambulance prior to hospital arrival, (3) were alive at the time of the EMS call but were deceased upon their arrival, or (4) emergency center walk-ins. Those under the age of 18 years, prisoners, injury onset > 24-h prior to arrival at first study site, bites, stings, other forms of envenomation, toxicologic injuries, drownings, patients who are found deceased on scene, and/or patients transported via private EMS (non-WCG EMS) will be excluded.

### Participant recruitment and informed consent

Eligible patients will be identified daily at all study sites. The clinical records of patients meeting inclusion criteria will be reviewed and data will be abstracted into the study database. Data for each patient will be linked as they traverse the emergency care system. Consistent with other observational emergency care studies, a waiver of informed consent was approved by the ethics boards to practically carry out this minimal risk research on patients with emergent (i.e., time-sensitive, and life-threatening) conditions.

### Variables, outcomes, and study measures

Epidemiologic information will be collected for each study participant for their entire clinical course at all associated study sites, including: patient demographic information (e.g., age, sex, race, and comorbidities); injury details (e.g., time, type, and intent); facility data (e.g., hospital name, trauma level, clinician qualifications, units of care); clinical data (e.g., vital signs, medications administered, critical interventions, operations performed); and, trauma system process (e.g., key dates and times [51]). Table 2 describes the exposures, predictors, and outcomes of interest in the EpiC study.

**Table 2 Tab2:** Key EpiC Study Exposure, Predictors, and Outcome Measures

Exposures	Definition	Variable Type	Data Source
1^O—^Critical resuscitative interventions (CRI)	Prehospital and in-hospital resuscitative interventions or therapeutics, delivered for the patient’s traumatic injury (e.g., thoracostomy for tension pneumothorax), within the first 24 h post-injury	Binary	EMS and/or Hospital
1^O^—Trauma-to-CRI time	Duration of time from injury to receiving a critical resuscitative intervention for the dominant injury	Continuous	EMS, Hospital, and/or Pathology

Predictors	Definition	Variable Type	Data Source
Age	Span of years lived at the time of injury	Continuous	EMS, Hospital, or Pathology
Sex	Biological sex given at birth	Categorical	EMS, Hospital, or Pathology
Comorbidities	One or more pre-existing disease or conditions present in the patient that are trauma-relevant chronic conditions (e.g., bleeding disorder)	Binary	EMS or Hospital
Socioeconomic status	Based on hospital insurance status	Categorical	Hospital
Mechanism of injury	Main force that created the injury or how injury was inflicted (e.g., firearm, Struck/hit, stabbing or cut, vehicular injury, fall, thermal, choking/hanging, iatrogenic, other)	Categorical	EMS, Hospital, or Pathology
Provider level	Health care provider qualifications (e.g., rank of EMS provider, type of doctor)	Categorical	EMS
Injury severity	ISS calculated as the sum of squares of 3 worst AIS scores. Low (< 12) or high (≥ 12)	Continuous, Binary	EMS, Hospital, or Pathology

Outcomes	Definition	Variable Type	Data Source
1^O—^Ambulance death or 7-day in-hospital mortality	All-cause mortality in the ambulance or within the hospital in the first 7-days post-injury	Time-to-event	EMS, Hospital, or Pathology
2^O^—30-day in-hospital mortality	All-cause mortality at any point during the hospital stay	Time-to-event	Hospital or Pathology
2^O^—Non-resuscitative surgical interventions	Post-injury interventional procedures such as fasciotomies, limb amputation, and laparotomies	Binary	Hospital
2^O^—Secondary infections	Post-injury infections such as wound infections, pneumonia, and sepsis	Binary	Hospital
2^O^—Organ failure	Organ failure will be assessed by individual organ (acute kidney injury, coagulopathy, and acute lung injury) and by a composite multiple organ failure score such the SOFA score up to 7-days	Continuous	Hospital

1^O^ = primary exposure or outcome; 2^O^ = secondary exposure or outcome; Data Source: EMS data is abstracted from WCG EMS Electronic Patient Care Reports, hospital data is abstracted from handwritten medical charts, and pathology data is abstracted from handwritten postmortem/autopsy reports from the Forensic Pathology Service of South Africa. EMS = Emergency Medical Services, ISS = Injury Severity Score, AIS = Abbreviated Injury Scale (anatomical score), SOFA = Sequential Organ Failure Assessment

The primary outcome of mortality will be defined as time to ambulance death or in-hospital death within 7 days of injury. The definition of examining mortality within 7 days was previously selected by a 20-person expert trauma panel to be the ideal duration to assess deaths for a study focused on the effects of early trauma resuscitation [52]. A study of three trauma-focused randomized controlled trials in urban U.S. settings have demonstrated that most hemorrhagic deaths occur in hospitals and within 6 h of patient encounter [51]. However, in our setting we examine a longer window since early deaths are more likely to occur at the scene due to the higher prevalence of penetrating injuries and fewer ambulance resources, and consequently later deaths will likely occur post-EMS transfer and hospital arrival. We will define the secondary outcomes of 24-h and 30-day mortality as time to in-ambulance or in-hospital mortality from injury. Other secondary outcomes include patients’ morbidity and need for operative interventions (those that are not considered damage control surgery), secondary infections (including wound infections, pneumonia, and sepsis), and organ failure (defined with the Sequential Organ Failure Assessment (SOFA) Score [53, 54]).

The primary exposures of interest are the delivery of CRI and trauma-to-CRI time. The delivery of CRIs will be defined as the performance of a resuscitative intervention (airway, breathing, circulatory, or neurologic) within the first 24-h from the time of injury. The trauma-to-CRI time will be defined as the duration from experiencing the injury to receiving a critical resuscitative intervention, which could occur at the trauma centre, a transferring hospital, or in the ambulance (in limited cases). To assess our secondary objective, we will additionally consider the individual resuscitative interventions as separate exposures of interest.

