## Statistical methods

Descriptive statistics will be estimated for all demographic, injury, facility, clinical, and systems process fields. Multivariable models will adjust for characteristics at the patient-level (e.g., age, sex, race, comorbidities, socio-economic status, injury mechanism, injury severity index) and provider-level (e.g., specialist trauma surgeon, general medical officer, advanced prehospital provider), as described in Table 2. Due to the small number of hospitals, site will be adjusted for as a fixed effect.

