### Assessing association with mortality outcomes

Time-to-event analyses will be used to estimate the association between delivery and trauma-to-CRI time with mortality outcomes. This approach allows us to (1) systematically follow a representative cohort of injured individuals that are alive at the initial request for medical attention with moderate to high baseline risks, and (2) produce valid estimates of the timeliness and effectiveness of the urgent care initiated within the regional trauma system for these individuals [57]. Multivariable Cox proportional hazards models with a time-dependent covariate for CRI will be used to study the effect of receiving CRI during different time periods post-injury (e.g., 0–2, 2–12, > 12 h). We will assess model fit and the proportional hazards assumption. We will consider alternative model specifications as necessary, including a left truncated Cox proportional hazards model [58, 59], joint modelling of CRI and death [60–62], and estimating the survivor average causal effect (SACE) [63–66].

The secondary objective of assessing the effect of the delivery and timing of individual resuscitative interventions that occur during clinical course will be evaluated using similar models. Some interventions are injury-specific, and thus analysis will be performed in appropriate subgroups (e.g., by injury type and injury severity).

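### The named adjusters contain no injury type or body region, and ISS does not separate head from limb injury, so head injury may confound the primary CRI and timing estimates

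*Protocol article*

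**What the plan says.** - **Collected data.** Under Variables, outcomes, and study measures, the article lists "injury details (e.g., time, type, and intent" among the items abstracted. Type is named; anatomical location is not.
- **Adjusters.** Statistical methods gives the patient-level adjusters, as examples, as "age, sex, race, comorbidities, socio-economic status, injury mechanism, injury severity index". It adds provider level, refers the reader to the predictors "as described in Table 2", and enters site as a fixed effect. The Table 2 predictors are age, sex, comorbidities, socio-economic status, mechanism, provider level and injury severity.
- **Severity.** Table 2 defines it as "ISS calculated as the sum of squares of 3 worst AIS scores. Low (< 12) or high (≥ 12", available from EMS, hospital or pathology records.
- **Mechanism.** Table 2 defines it as "Main force that created the injury or how injury was inflicted".
- **Primary exposure.** Delivery of CRI is the "performance of a resuscitative intervention (airway, breathing, circulatory, or neurologic) within the first 24-h from the time of injury". Table 2 measures trauma-to-CRI time to the intervention for the dominant injury.
- **Use of injury type.** For the secondary objective on mortality: "Some interventions are injury-specific, and thus analysis will be performed in appropriate subgroups", with injury type and severity as the examples. The morbidity section has a parallel sentence, also under the secondary objective.

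**The concern.** The primary exposure is any intervention from four clinical domains. Which one is indicated depends on what is injured, and the article itself says that some interventions are injury-specific. If body region also affects the risk of death at a given ISS, it is a common cause of exposure and outcome.

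Neither severity nor mechanism, as defined, closes that path. ISS is a single sum with no region term. Mechanism describes the force applied, and a fall, a blow or a collision can injure any region. Subgroups by injury type protect the analyses of individual interventions, but not the pooled any-CRI and timing estimates of the first objective.

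At stake is whether the primary hazard ratio reflects early treatment or partly a different mix of head-injured and other patients. The study is powered for a hazard ratio of 0.85, so a modest bias is enough to matter.

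**Working it through.** **1. The plan's own figure.** Inputs from Power calculation: 14,400 cases, 10% 7-day mortality, 30% with CRI within 2 h, two-sided alpha 0.05, 80% power.

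- Events expected: 14,400 × 0.10 = 1,440.
- Events needed (Schoenfeld): (1.960 + 0.842)² / [0.30 × 0.70 × (ln 0.85)²] = 1,416.
- Power with 1,440 events: 0.807. Detectable HR: exp(−2.802 / √(1,440 × 0.21)) = 0.851.

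The stated 0.85 reproduces. It serves here only as a yardstick; the point is about confounding, not power.

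**2. ISS and region.** By the Table 2 formula, an isolated AIS 4 head injury scores 4² = 16, and so does an isolated AIS 4 limb injury. Both fall in the high class (12 or more).

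**3. Size of possible bias.** The 30% and 10% margins come from the article. The rest is assumed: 20% of patients have a severe head injury, CRI has no effect, and head injury multiplies 7-day mortality by R at equal ISS.

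Case A: 20% of head-injured and 32.5% of other patients receive CRI within 2 h (overall 0.2 × 20% + 0.8 × 32.5% = 30%).
- Head injury among early: 0.2 × 0.20 / 0.30 = 13.3%.
- Head injury among not early: 0.2 × 0.80 / 0.70 = 22.9%.

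Case B (imbalance reversed): 40% and 27.5% (overall 0.2 × 40% + 0.8 × 27.5% = 30%).
- Head injury among early: 0.2 × 0.40 / 0.30 = 26.7%.
- Head injury among not early: 0.2 × 0.60 / 0.70 = 17.1%.

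Apparent risk ratio = [1 + p₁(R − 1)] / [1 + p₀(R − 1)], where p₁ and p₀ are the head-injury shares among early and not-early patients.

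| R | Case A | Case B |
|---|---|---|
| 1.5 | 1.067 / 1.114 = 0.96 | 1.133 / 1.086 = 1.04 |
| 2 | 1.133 / 1.229 = 0.92 | 1.267 / 1.171 = 1.08 |
| 4 | 1.400 / 1.686 = 0.83 | 1.800 / 1.514 = 1.19 |

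Check at R = 4: mortality of 25% with and 6.25% without head injury gives 0.2 × 25% + 0.8 × 6.25% = 10% overall. Case A is then 8.75% v 10.54%, and Case B 11.25% v 9.46%.

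**4. Effect on error rate.** Take assumed head-injury shares of 20% v 30% with R = 2. The apparent HR is 1.2 / 1.3 = 0.923. With 1,440 events, a true null is rejected in that direction about 29% of the time, against a nominal two-sided 5%.

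**5. Price of adjusting.** Replace 1,440 events by 1,440 × (1 − R²), where R² is the assumed share of exposure variance explained by the added term. The detectable HR moves from 0.851 to 0.848, 0.844 or 0.835 for R² of 0.05, 0.10 or 0.20.

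**The case against.** The strongest reply is that the adjuster list is open. It is introduced as examples, Table 2 is headed as key measures, and the two lists differ: race and site are adjusters but not Table 2 predictors. A condensed article may leave the full covariate list to an analysis plan. A reader might infer that body region has been ruled out of the models; the text does not say so. What remains is that the list points to Table 2, that neither contains type or region, and that injury type is given an explicit role elsewhere, confined to the secondary objective. Following the plan as stated leaves the gap.

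A reader might also infer that injury location is already recorded as a study variable. The article names only type, which it does not define and which may overlap with mechanism. Location is an inference from the AIS coding that ISS requires.

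The calculation is fairly criticised as well. It is a crude risk ratio between fixed groups at equal ISS, not the planned Cox model with time-dependent CRI. Age, mechanism, provider level and site would absorb part of the imbalance; mechanism, for example, partly separates penetrating from blunt injury. None of the listed adjusters identifies head injury.

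Finally, the authors have not overlooked injury type: the timing definition and the planned subgroups recognise it. That does not protect the pooled primary estimates.

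**Conclusion.** The point stands as plausible residual confounding that the named adjustment set does not address. It is not a demonstrated bias. It is tempting to conclude that the primary hazard ratio will be distorted by about as much as the 0.85 target. The documents do not support that: ratios of 0.83 and 1.19 need a fourfold mortality ratio at equal ISS, which is an assumption. At a twofold ratio the distortion is 0.92 or 1.08, and at 1.5-fold it is 0.96 or 1.04. The head-injury prevalence and the split of early treatment are assumed too.

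The direction is unknown, so the bias cannot be called conservative. The change is worth making because the term is cheap and can be derived from coding the study already needs. The open list and the possibility of a fuller analysis plan make this a recommended improvement, not a fatal defect.

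**What to change.** Add to Table 2, and to the primary mortality and morbidity models, a head-injury indicator (for example head AIS of 3 or more), the dominant injury region, or both. Keep ISS alongside. If hazards are not proportional by head injury, use it as a Cox stratum.

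Derive the variable from the same AIS coding and the same sources as ISS: EMS, hospital or pathology. Do not restrict it to clinical records. Ambulance and on-arrival deaths are eligible, and some may have their injuries documented only at autopsy. The primary analysis is complete-case on predictors, so a clinical-records-only covariate could drop these early deaths selectively. State that missing region must not remove such deaths from the primary analysis, and show a sensitivity analysis by source of the AIS coding.

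The cost is some analysis-plan wording, a few degrees of freedom and a small loss of precision: a detectable HR of about 0.85 to 0.84 for an assumed R² of 0.05 to 0.20. If the AIS codes are held as ISS requires, no new data collection should be needed.
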